### Blinding

Study personnel responsible for survey administration and/or data analysis will be blind to participant condition and are not unblinded. Participants will not be blinded as it was not possible to create a “sham” digital intervention and coaching program.

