#### Participant randomization

We will randomize at the level of the patient. While this poses a modest risk of provider contamination between intervention and control participants, providers will not receive any communication from the study team after enrollment. We have further addressed the potential effect of contamination by increasing sample size, allowing detection of smaller intervention effects.

Participants will be stratified by 4 demographic groups (Cantonese-speaking, Spanish-speaking, Black/African American English-speaking, and multi-cultural English-speaking) and randomly assigned 1:1 to either the INSPIRE intervention (Group 1) or control groups (Group 2). The CRC will utilize random block randomization to maximize balance between treatment groups throughout accrual while ensuring the randomization sequence remains unpredictable. A random allocation sequence was generated using a computer, where treatment groups were labeled as Group 1 or 2. After participants consent to study participation and complete baseline measures, clinical research coordinators will assign the next available study ID number in sequence, identify the allocated group, and inform participants of their assignment. The study ID number and Personal Health Information (PHI) will be stored in a HIPAA-compliant manner (REDCap) along with the intervention assignment (Group 1 or 2). Study personnel responsible for outcome evaluations will be blinded to which Group 1 or 2 represents.

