### Study onboarding

When participants assigned to Group 1 (INSPIRE intervention) are notified of their assignment, they receive language concordant email instructions regarding how to download and access the INSPIRE mobile application from the Apple or Google Play (i.e., Android) app stores and are instructed how to access the INSPIRE intervention website using any standard browser for participants who prefer a website to an app. For those in Group 1, a CRC also emails a brief biography of their assigned health coach. The assigned coach calls the participant to schedule the Week 0 session which is held on a remote video platform (Zoom) and reminds them to download and login to the app before the Week 0 meeting. To better support and engage patients with limited tech literacy, the Digital Health Literacy Instrument will be administered at baseline to identify Group 1 participants that may need extra technical support [96]. For those with low digital literacy or if the participant demonstrates technical issues with the app or is unfamiliar with Zoom during the onboarding session, the coach provides brief technical support and troubleshooting over the phone. If additional support is needed, the coach schedules a tech support meeting with the participant and the CRC who uses instructional videos and 1×1 “tech tutoring” sessions.

For participants assigned to Group 2 (waitlist controls), the CRC emails the INSPIRE Workbook pdf or mails a print copy if requested. Onboarding for Group 2 will include sharing and introducing the INSPIRE intervention manual (print or pdf) via a one-time hour-long video session. CRCs call the participant to schedule the workbook orientation, walk through the table of contents, and encourage participants to explore and use the manual on their own.

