#### Participant retention, adherence, and engagement

Given the challenges often faced by our target population and the limitations caused by chronic pain, substantial attention and support will be provided to maximize participant retention and completion of survey instruments at all time points. Text, email, and/or phone call reminders from CRCs will be used to remind participants of assessments and to provide the relevant survey link to REDCap. Non-adherence will be addressed by coaches within the telehealth sessions to better understand and address obstacles to survey completion.

In accordance with Good Clinical Practice (GCP) and International Council for Harmonisation (ICH) guidelines, all participants retain the right to withdraw from the clinical trial at any point. Discontinuation from trial intervention does not mean discontinuation of the study altogether, and the remaining study procedures, follow-up assessment/visits, and data collection will be completed as indicated in the protocol (unless consent is specifically withdrawn).

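### The blinding claimed for survey staff and analysts is contradicted by the coordinators' described tasks and by a group code whose key is printed

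*Protocol article*

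**What the plan says.** The Blinding section of the protocol article makes an unqualified claim: "Study personnel responsible for survey administration and/or data analysis will be blind to participant condition and are not unblinded". It adds that participants are not blinded, because no sham app and coaching programme could be made. Participant randomization supplies the only masking device: "Study personnel responsible for outcome evaluations will be blinded to which Group 1 or 2 represents".

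Other sections describe who does what.

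- **Allocation (Participant randomization).** Once consent is given and the baseline data are in, "clinical research coordinators will assign the next available study ID number in sequence, identify the allocated group, and inform participants of their assignment". Assignments are held in REDCap with the study ID and identifying data.
- **Meaning of the label (Participant randomization).** Participants are "randomly assigned 1:1 to either the INSPIRE intervention (Group 1) or control groups (Group 2".
- **Onboarding, INSPIRE arm (Study onboarding).** "For those in Group 1, a CRC also emails a brief biography of their assigned health coach". A CRC also gives individual technical tutoring where it is needed.
- **Onboarding, control arm (Study onboarding).** The CRC sends the workbook, and "CRCs call the participant to schedule the workbook orientation".
- **Survey contact (Participant retention, adherence, and engagement).** "Text, email, and/or phone call reminders from CRCs will be used to remind participants of assessments", and the same contact carries the REDCap survey link. Coaches are to take up non-adherence in their telehealth sessions, including whatever hinders participants from completing surveys.

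**The concern.** A role that tells participants their arm and then delivers arm-specific onboarding is not blind to condition. The article names no other role for survey contact. A label does not mask anyone who can read its definition, and Study onboarding uses Group 1 and Group 2 as working names for the arms.

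Two things are at stake. The first is follow-up. The primary mixed model relies on data being missing at random, and staff who know the arm, with coaches helping in one arm only, may influence who returns a 3-month PEG. The second is analysis. Primary analysis of the primary endpoint leaves the form of time to be chosen from a graph of the outcome, and lets baseline covariates found to be imbalanced enter the model. Analyst blinding would protect those choices, and readers of the trial report would credit it on the strength of the Blinding section.

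**Working it through.** No stated figure depends on this point, so the check is a side-by-side reading, with one piece of arithmetic for scale.

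**1. Survey staff**

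| Task | Role named | Does the task reveal the arm? |
|---|---|---|
| Identify and disclose allocation | CRC | Yes |
| Coach biography and technical tutoring | CRC | Yes, INSPIRE only |
| Workbook and its orientation | CRC | Yes, control only |
| Survey reminders and REDCap link | CRC | The arm is already known to this role |
| Help with survey completion | Coach | Yes, INSPIRE only |

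Every role named in connection with surveys is one that knows the allocation. At role level, the claim in the Blinding section has nobody to attach to.

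**2. The label.** Masking by Group 1/2 works only if evaluators lack the key. Participant randomization prints the key and Study onboarding uses it. The article describes no second, neutral code for the analysis file.

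**3. Data that reveal the arm regardless of the code.** Study measures lists app module completion, log-ins and coaching attendance. Under Waitlist control condition, controls are offered the app only after 12 months and get no coach, so during the trial these data arise in the INSPIRE arm only. Table 1 schedules the Mobile App Rating Scale at 3 months, the primary time point, when only the INSPIRE arm has the app. The nonadherence analysis under Secondary analyses of the primary outcome needs adherence data. An analyst who holds these variables with the outcome file can recover the arms under any code.

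**4. Asymmetry of follow-up.** Coaching is weekly for 3 months, so INSPIRE participants have a second person raising survey completion up to the primary assessment. Booster sessions at months 5 and 11 fall one month before the 6- and 12-month surveys. Controls have one orientation visit and no coach.

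**5. Scale.** Sample size justification gives 586 enrolled (293 per arm) and 73% retention.

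- Expected without a 3-month PEG: 586 × (1 − 0.73) = 586 × 0.27 = 158.2, about 158 participants.
- Per arm, if loss were equal: 293 × 0.27 = 79.1, about 79.

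This is the number whose response could be affected by differential prompting. It is not an estimate of bias. On the analysis side, four forms of time are open (linear, quadratic, two-piece, categorical) before a test at 0.05, plus an unspecified set of imbalance covariates.

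**The case against.** The strongest reply is that CRC is a role filled by several people. No section says that the individual who randomises or onboards a participant also handles that participant's surveys, and the article condenses a fuller protocol and mentions an operations manual, where rostering and recoding might sit. This stands as far as it goes. A reader might infer that the blinding does not exist at all, or that CRCs cannot be blind; the documents do not establish that. They do show that the claim as written conflicts with the roles and coding described.

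A reader might also infer that CRCs collect the PEG answers. The text describes a reminder and a link, which points to self-completion; no section has a CRC taking PEG responses by telephone. One can argue that sending a link is not administering a survey. That narrows the contradiction but leaves the article naming no other survey staff.

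It would be tempting to call staff and analyst blinding the only protection left. It is not. Participants rate their own PEG knowing their arm, so blinding the sender of a link does little against that bias, while randomisation, intention-to-treat analysis and a single named 3-month contrast remain in place.

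On the analyst, Data management lists the data analyst separately from the CRCs, and nothing gives the analyst participant contact or the allocation list. The case here rests on the printed key and the arm-revealing variables, and is weaker than the case on survey staff. A neutral code would not replace fixing the model in advance either: an analyst viewing outcome graphs by arm could guess which arm is which. The analysis plan, which is not shown, may already fix those choices.

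**Conclusion.** The statement in the Blinding section is contradicted by the article's own account of CRC tasks, coach involvement and group labels, and should be corrected. The risk is limited to two routes: survey prompting and retention that differ by arm, with about 158 of 586 participants expected to lack a 3-month PEG at the stated retention; and choice of the form of time and of imbalance covariates by someone who can tell the arms apart. Neither the size nor the direction of any bias can be computed from the document. The primary test remains valid in form.

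The conclusion assumes that the article's role descriptions reflect practice and that no unshown document separates CRC duties or recodes the arms. If one does, what remains is a wording correction.

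**What to change.** 1. **Analyst.** Supply a neutral arm code unrelated to Group 1/2, in a file without app-usage, coaching or app-rating variables, until the form of time and the covariates of the primary model are fixed. Release those variables afterwards for the nonadherence and mediation analyses.
2. **Reminders.** Make identical automated REDCap reminders the default in both arms, with the same escalation schedule for non-responders.
3. **Text.** Restate the Blinding section: participants, coaches and CRCs are unblinded, and blinding is claimed only for named staff with no access to allocation. Drop or explain the sentence on masking by Group 1/2.

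Having different CRCs handle onboarding and survey contact is optional where staffing allows. The article does not give the number of CRCs, and screening staff must be language-concordant across three languages, so feasibility is not shown.

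Timing limits what can be changed. Recruitment began on April 28, 2025 and the article appeared on January 8, 2026, so participants enrolled before about October 2025 had by then reached their 3-month assessment. The second change helps only later assessments. The third can cover the whole trial, and so can the first if the analyst has not yet worked with the arms identified.

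The cost is minor REDCap set-up, recoding one variable, and a less favourable blinding statement.

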### Study onboarding

When participants assigned to Group 1 (INSPIRE intervention) are notified of their assignment, they receive language concordant email instructions regarding how to download and access the INSPIRE mobile application from the Apple or Google Play (i.e., Android) app stores and are instructed how to access the INSPIRE intervention website using any standard browser for participants who prefer a website to an app. For those in Group 1, a CRC also emails a brief biography of their assigned health coach. The assigned coach calls the participant to schedule the Week 0 session which is held on a remote video platform (Zoom) and reminds them to download and login to the app before the Week 0 meeting. To better support and engage patients with limited tech literacy, the Digital Health Literacy Instrument will be administered at baseline to identify Group 1 participants that may need extra technical support [96]. For those with low digital literacy or if the participant demonstrates technical issues with the app or is unfamiliar with Zoom during the onboarding session, the coach provides brief technical support and troubleshooting over the phone. If additional support is needed, the coach schedules a tech support meeting with the participant and the CRC who uses instructional videos and 1×1 “tech tutoring” sessions.

For participants assigned to Group 2 (waitlist controls), the CRC emails the INSPIRE Workbook pdf or mails a print copy if requested. Onboarding for Group 2 will include sharing and introducing the INSPIRE intervention manual (print or pdf) via a one-time hour-long video session. CRCs call the participant to schedule the workbook orientation, walk through the table of contents, and encourage participants to explore and use the manual on their own.

### Trial interventions

#### INSPIRE Intervention: conceptual background/model

INSPIRE’s conceptualization of CP is grounded in the biopsychosocial (BPS) model that highlights the interplay of biological (e.g. genetic vulnerability, physical health, tissue damage), psychological (e.g. emotional distress, attention, cognition), and social factors (e.g. social location, social determinants of health, culture) [27]. Stigma, bias, and other drivers of disparities are part of the BPS model which informed the development of this intervention. The social-ecological model of CP shown in Fig. 2 highlights select variables thought to play a role in disparities and influenced by the INSPIRE intervention.

**Fig. 2 Fig2:**
[figure not shown]
Social-ecological model of chronic pain

#### Intervention development

Throughout the development process, we applied a human-centered design (HCD) approach that focuses on the usability and needs of those the intervention is meant to serve including B/AA, Latinx, and Chinese patients. Digital health solutions that use HCD to incorporate the patient and clinician voice and account for their workflows can augment digital tools to deliver high-quality and personalized care in routine practice and can be particularly valuable in designing interventions for HDPs [99–108]. We first used stakeholder focus groups applying HCD principles to create the INSPIRE patient-facing app and data collection tool. Brief alpha and beta testing occurred after the formative focus groups, followed by a 3-month feasibility and acceptability pilot to further test the app functionality and tailoring. As a final assessment of intervention fidelity to our evidence-based interventions (i.e., CBT, MBI, MFI), we assembled an independent “Clinical Science and Practice Advisory Board” to review and approve the content. This board was comprised of local pain management clinicians, including a pain medicine physician, psychologist, pharmacist, physical therapist, and the director of the ZSFG pain management service.

#### INSPIRE intervention: mobile app

The INSPIRE intervention includes a participant-facing mobile app that delivers 12 weekly, integrative treatment modules which combine aspects of CBT, MBI, MFI, and a personal, telehealth coach who will meet with the participant weekly for 3 months. App content also includes an education “library,” tools for “quick relief” (i.e., acute exacerbations of pain), a community bulletin board, and a “favorites” section that the participant and coach will use to create a tailored pain management plan. All INSPIRE intervention participants will receive “booster sessions” with their coach at months 5 and 11 to review pain management skills and re-visit key modules within the mobile app. Throughout the 12-month study, intervention participants can complete and view their own patient-reported outcome (PRO) data (e.g., PEG, PHQ-8, GAD-7) to self-monitor their progress via the INSPIRE app. A brief outline of the 12 modules can be found in Table 2. A screenshot of the app’s homepage is listed in Additional file 3.

**Table 2 Tab2:** INSPIRE intervention modules

**Session**	**Topic**	**Focus of coaching session**
0	Introduction	Introductions, building rapport, identifying goals
1	Mind-body and pain introduction	Introduction of nonpharmacologic interventions, rapport building, norm setting
2	Mindfulness and CBT	Mindfulness skills, CBT introduction (“Thinking about Thinking”)
3	Movement	Movement education, mind and movement, exercise
4	Stress and Chronic Pain	Definition of stress, coping skills, getting out of your head
5	CBT Deep Dive #1	“ABC” Model; Thoughts and feelings, behaviors and feelings
6	CBT Deep Dive #2	Cognitive restructuring and mastering thoughts, flexibility; ABCD exercises
7	Sleep	Sleep education, insomnia and chronic pain, sleep assessment; sleep meditations
8	Building Self-Efficacy for Pain Management	Self-efficacy, self-compassion; Loving-Kindness Meditation
9	Mindfulness and Movement	Catastrophizing and mindfulness, exercise and aerobic training, movement meditations
10	Social Connections and Community	Social support, isolation and loneliness, support circle, mindful communication
11	Building your Toolbox	Gratitude, Yoga, Tai Chi, positive emotions, savoring
12	Reinforcing skills and practicing for the future	Building/revising pain plan, review key skills, self-care/compassion, guided reflection, find your community

Outlines the focus and topic of each coaching session delivered to participants during the 12-week intervention period, including the baseline session at Week 0. Each weekly session covered a distinct theme aligned with the study’s intervention goals. The content was structured to support behavior change and skill development relevant to the primary and secondary outcomes of the trial

#### INSPIRE intervention: health coaches

This innovative intervention element will include a one-hour orientation/introduction to the program followed by 12 weekly telehealth coaching calls to patients guided by PRO scores and module completion data summarized in the coach’s dashboard. One-hour booster sessions will be delivered at months 5 and 11. The exact roles and expectations of the coaches were determined by current best practices of multiculturally validated programs, patient preferences, and provider/clinic/system needs, with all duties and procedures summarized in a detailed coaching manual [74, 109–115]. We anticipate one PhD-level clinician will serve as the lead coach that supervises 4–5 additional coaches using the UCSF coaching model with a digital patient registry and online dashboard to track participant progress [116].

Coaches will utilize a manual to standardize content facilitation for each week’s materials. Coaches take notes, help patients establish goals, follow their progress, and problem solve issues around intervention engagement and adherence. Coaches were trained for over 80 hours using didactics, role plays, and video review with feedback and remediation when necessary. Coaches will direct participants to their PCP regarding medications, referrals to specialty care, and to address urgent medical issues, and will report AE’s to the study PI and coordinator.

#### Waitlist control condition

Participants randomized into the control condition will continue to receive any interventions from their medical team currently deemed the current standard of care for CP at UCSF/SFHN. Control participants will also receive a printed or pdf manual of the INSPIRE mobile app modules in their preferred language plus one telehealth visit to orient them to the manual. After participants complete the 12-month study, they will be invited to download the INSPIRE app and given access to the INSPIRE intervention website, which they can work through on their own. Participants will not work with a pain management coach due to limited funding to support coaches during and after the RCT. A waitlist control condition was chosen in order to promote participant retention and to address concerns about equity raised by the recruitment clinic directors.

## Outcomes and study measures

### Study measures

Participants will be asked to complete surveys at baseline and at 3, 6, and 12 months. Measures were selected based on the HEAL Common Data Elements and our hypothesized INSPIRE treatment effects pathway model (Fig. 3) [83]. Instruments were translated to Spanish and Chinese (traditional) when necessary and validated when possible. All published measures are cited in Table 1. Adherence with the INSPIRE intervention will be measured with app usage data including module completion rates and log in times, and attendance for coaching sessions. We will collect demographic information including age (in years), race, ethnicity, level of education, employment status, and annual household income as noted in Additional file 4. Other characteristics will include disability insurance, rural-urban commuting area code, and duration of pain.

**Fig. 3 Fig3:**
[figure not shown]
INSPIRE Treatment Effects Pathway Model

### Primary outcome

The primary outcome will be Pain, Enjoyment, and General Activity (PEG) score at 3 months. The PEG is a validated 3-item pain assessment tool measuring self-reported pain intensity (P) and interference with enjoyment (E) and general activities (G); items are rated 0–10, with the final PEG score averaging responses over 3 items, with a range of 0–10 [80, 117]. Higher values correspond to worse pain experience and interference.

